# A randomized phase II trial on the addition of dutasteride to combined androgen blockade therapy versus combined androgen blockade therapy alone in patients with advanced or metastatic salivary duct carcinoma – the DUCT study protocol

**DOI:** 10.1186/s12885-024-12889-0

**Published:** 2024-09-20

**Keywords:** Rare Cancer, Salivary Duct Carcinoma, Androgen Receptor, Combined Androgen Blockade, Androgen Deprivation Therapy, Dutasteride, Steroid 5α-reductase, Anti-hormonal therapy, Systemic therapy, Salivary gland cancer

## Abstract

**Background:**

Salivary duct carcinoma (SDC) is a rare and aggressive subtype of salivary gland cancer, frequently associated with incurable recurrences and distant metastases (R/M). Proliferation of SDC relies on androgen receptor (AR) signalling, prompting the use of combined androgen blockade (CAB, *i.e.*, luteinizing hormone-releasing hormone agonist and/or AR antagonists) to R/M SDC patients. However, only a subset of patients benefits from such treatments. We have shown that response to CAB is associated with *steroid 5α-reductase 1* (*SRD5A1*) mRNA expression. SRD5A1 catalyses the intracellular conversion of testosterone into the more potent AR-agonist dihydrotestosterone. This conversion can be inhibited by dutasteride, a potent SRD5A1-inhibitor, which is currently prescribed for benign prostatic hyperplasia. We hypothesize that repurposing dutasteride to target AR signalling in SDC could enhance therapeutic response and clinical outcome in SDC patients.

**Methods:**

This prospective, open-label, randomized controlled phase II clinical trial, is designed to investigate whether dutasteride as an adjunct drug to CAB improves response rate and clinical outcome in patients with AR-positive R/M SDC. Patients are divided in two cohorts based on their prior systemic treatments. In cohort A, CAB-naïve patients (*n* = 74) will be randomly assigned to either a control arm (Arm 1) receiving CAB (goserelin 10.8 mg/3m and bicalutamide 50 mg/OD) or an experimental arm (Arm 2) where dutasteride (0.5 mg/OD) is added to the CAB regimen. In cohort B, patients with disease progression after adjuvant or first-line palliative CAB therapy (max. *n* = 24) will receive goserelin, bicalutamide, and dutasteride to assess whether the addition of dutasteride can overcome therapy resistance. The primary endpoints are the objective response rate and duration of response. Secondary endpoints are progression-free survival, overall survival, clinical benefit rate, quality of life, and safety. Translational research will be performed to explore molecular target expression differences and their correlation with clinical outcome.

**Discussion:**

The DUCT study addresses an unmet medical need by investigating the repurposing of dutasteride to enhance treatment response and improve clinical outcome for patients with R/M SDC, especially those with limited alternative treatment options, such as HER2-negative cases. By repurposing a registered low-cost drug, this trial’s findings could be readily applied into clinical practice.

**Trial registration:**

Clinicaltrials.gov Identifier: NCT05513365. Date of registration: August 24, 2022.

**Protocol version:**

Current protocol version 4.0, February 21, 2024.

## Background

Salivary gland cancer (SGC) is a rare cancer, exhibiting an annual incidence of approximately 1 to 2 new cases per 100,000 individuals [1, 2]. The World Health Organization (WHO) classifies over twenty malignant epithelial salivary gland tumour types based on histological and clinical features [3]. Salivary duct carcinoma (SDC), represents one of the most aggressive subtypes, predominantly affecting the parotid gland [2]. In SDC, incurable local recurrences and/or distant metastases (R/M) are common and treatment options are limited, especially when human epidermal growth factor 2 (HER2) status is negative or when no other druggable genetic alterations are present in the tumour [3–5]. Half of all patients already present with locoregional or distant metastases at diagnosis or will develop metastases throughout the course of their disease [6]. Distant metastases are predominantly present in the lungs (54% of patients with distant disease), bones (46%), and brain (18%) [2]. The median overall survival (OS) in R/M SDC is only 5 months when best supportive care is given [7].

SDC, like prostate cancer (PCa), relies on the androgen receptor (AR) signalling pathway for tumour growth, and therefore androgen-receptor signalling inhibitors (ARSI) and androgen deprivation therapy (ADT) have been studied [2, 8]. In a phase II trial, the efficacy of combined androgen blockade (CAB), consisting of a luteinizing hormone-releasing hormone (LHRH) agonist (*i.e.,* leuprorelin acetate 3.75 mg/4w) in combination with an anti-androgen (*i.e.*, bicalutamide 80 mg/OD) has been studied in advanced SDC patients. The objective response rate (ORR) was 42% (11% complete response (CR) and 31% partial response (PR)), median progression free survival (PFS) and OS were 8.8 months and 30.5 months, respectively [4]. Based on this trial and retrospective case series, the ASCO guidelines [9] and the ESMO guidelines [6] strongly recommend to treat AR-positive R/M SDC patients with CAB. Still, there remains an unmet clinical need for improvement of current anti-hormonal treatments and/or novel systemic treatment strategies, but the rarity of SDC hampers the performance of large clinical trials.

Previous translational research has demonstrated that high levels of *SRD5A1* mRNA, encoding for the 5-alpha reductase type 1 enzyme, is predictive for clinical benefit and prolonged PFS and OS in CAB-treated AR-positive SDC patients [10]. SRD5A1 catalyses the intracellular conversion of testosterone into the more potent AR agonist dihydrotestosterone. Based on this mechanism, it is hypothesized that patients with high *SRD5A1* levels are highly dependent on androgens for their survival, and hence, benefit more from AR-targeting therapies. Notably, both isoforms of 5-alpha reductase, type I and type II, are inhibited by dutasteride, an oral anti-androgenic compound. In clinical practice, dutasteride has been approved for the treatment of benign prostate hyperplasia, a prevalent condition in elderly men. The extensive experience with prolonged use of dutasteride has demonstrated a relatively-well tolerability with a low incidence of (severe) side-effects [11]. In addition to the current approved indication, the efficacy of dutasteride has been investigated in several PCa trials. In a randomized placebo-controlled phase II trial, the efficacy of dutasteride monotherapy was evaluated in 294 patients with advanced PCa. Dutasteride significantly delayed the time to prostate-specific antigen (PSA) doubling compared with placebo after 2 years of treatment, along with suppressed tumour growth demonstrating an overall relative risk reduction of 59% in favour of dutasteride compared to placebo (*p* < *0.001*) [12]. The combination of a 5-alpha reductase inhibitor and CAB has also been studied in PCa, indicating that dutasteride in combination with anti-androgens could be of added value in localized or even locally advanced PCa [13–16]. For example, in a randomized clinical trial, 59 patients with localized PCa have been treated with an LHRH agonist and an anti-androgen with or without the 5-alpha reductase inhibitor finasteride. Notably, patients treated with CAB plus finasteride exhibited a significantly longer median time to relapse based on their PSA increase (34 months) compared to patients receiving CAB alone (19 months; *p* = *0.013*) [14, 15]. Recently, dutasteride has been investigated as a second-line therapy in combination with abiraterone in two patients with abiraterone-resistant PCa. Although limited to a sample size of two, the results suggests that dutasteride may improve the clinical efficacy of abiraterone in abiraterone-resistant PCa [17]. Furthermore, an in vitro study demonstrated a synergistic inhibition of prostate tumour cell proliferation by combining a 5-alpha reductase inhibitor and an AR antagonist [18].

Based on the overexpression of *SRD5A1* in CAB-responsive R/M SDC, and the efficacy of dutasteride in several trials involving men with prostate cancer, dutasteride could also be a valuable addition to the armamentarium against SDC. Hence, these findings provide a rationale for considering dutasteride as an adjunct drug to CAB therapy, offering a promising novel treatment approach to improve therapy response and clinical outcomes in patients with this aggressive rare cancer (Fig. 1). To date, no clinical trials have been conducted to assess the efficacy and safety of dutasteride as an adjunct drug in SDC patients undergoing anti-hormonal therapy. Here, we detail a prospective, open-label, randomized controlled phase II clinical trial, designed to investigate whether dutasteride as an adjunct drug to CAB improves therapy response and clinical outcome in patients with AR-positive R/M SDC.

**Fig. 1 Fig1:**
[figure not shown]
Simplified version of the androgen receptor pathway in salivary duct carcinoma, including the androgen-receptor signalling inhibitors under investigation in the DUCT study. The uncertain interaction between the HER2 receptor and AR is represented by the dotted grey arrows. Abbreviations: ACTH, adrenocorticotropic hormone; AR, androgen receptor; DHT, dihydrotestosterone; HER2, human epidermal growth factor 2; LH, luteinizing hormone; LHRH, luteinizing hormone-releasing hormone; SDC, salivary duct carcinoma; SRD5A1, 5α-reductase 1; TP53, tumour protein p53

## Objectives

The primary objectives of the DUCT study are to evaluate the ORR of dutasteride in combination with CAB patients with R/M SDC together with the duration of response (DoR), and to evaluate whether addition of dutasteride counteracts therapy resistance in patients who previously have been treated with anti-hormonal therapy. The ORR is defined as the proportion of participants who have CR or PR determined per RECIST v1.1. The DoR is defined as the time from first tumour assessment at which the objective response was recorded as CR or PR that is subsequently confirmed until PD determined per RECIST v1.1, or death from any cause, whichever occurs first.

The secondary objectives are:To assess the PFS, defined as the time from trial enrolment until date of first documented disease progression per RECIST v.1.1, or death due to any cause, whichever occurs first.To assess the OS, defined as the time from trial enrolment to the date of death due to any cause.To assess the clinical benefit rate (CBR), including confirmed CR or PR at any time or stable disease (SD) of at least 6 months determined per RECIST v.1.1.To assess the quality of life (QoL) of patients treated with anti-hormonal therapy, according to approved EORTC (QLQ-C30, QLQ-H&N43, QLQ-SHQ22) and VAS questionnaires.To assess the safety profile of dutasteride combined to CAB therapy by the incidence of severe adverse events (SAE) according to National Cancer institute Common Terminology Criteria for Adverse Events (NCI-CTCAE) version 5.0.To explore expression of molecular markers (*e.g., AR*, *SRD5A1* and *SRD5A2*) in patients’ blood and tumour samples to monitor treatment efficacy.

## Methods

### Trial design

The DUCT study is a prospective, open-label, randomized controlled, single-institution (Radboud university medical center; Radboudumc, Nijmegen, The Netherlands), phase II clinical trial, to investigate the efficacy of dutasteride as an adjunct drug to CAB in AR-positive R/M SDC patients. The trial is approved by the Medical research Ethics Committees United (MEC-U) as of August 11, 2022 by Clinical Trials Information System (CTIS) portal [reference EU CT-number: 2022–500745–24–00] and is registered on ClinicalTrials.gov [NCT05513365; date of registration August 24, 2022]. This protocol adheres to the Standard Protocol Items: Recommendations for Interventional Trials (SPIRIT) guidelines [19].

The DUCT study is divided in two cohorts according to prior systemic treatment(s) (Fig. 2). In cohort A, CAB-naïve patients (*n* = 74) will be randomized in a 1:1 ratio, in which the control arm will receive goserelin (10.8 mg/3m) and bicalutamide (50 mg/OD), and the experimental arm will receive goserelin (10.8 mg/3m), bicalutamide (50 mg/OD), and dutasteride (0.5 mg/OD). In cohort B, CAB-resistant patients (*n* = max. 24; *e.g.*, in the adjuvant setting with anti-androgens and/or LHRH-analogues or in the palliative R/M setting progressive on first-line therapy) will be enrolled receiving similar therapy to the experimental arm, *i.e.*, goserelin, bicalutamide, and dutasteride.

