### Cohort B – CAB-resistant patients

The Simon’s two-stage design, optimal version, will be applied for enrolment in cohort B [28]. The null hypothesis that the true ORR is 5% will be tested against a one-sided alternative, as prior data indicate that the response rate on second-line chemotherapy in patients with SGC is 5% [29]. The combination of the triple therapy will be considered effective and worth of further evaluation if the ORR is at least 20%. In the first phase, nine participants will be accrued and if in at least one of these nine participants a partial or complete response will be observed, fifteen additional participants will be accrued in the second phase of enrolment to a final overall sample size of 24 participants. In case no responses are observed in the first nine patients, cohort B will be closed early for futility. If at least three out of 24 participants confirmed responses are observed, the null hypothesis will be rejected in favour of this triple therapy and this therapy will be considered promising and worthy of further investigation. This design yields a type I error rate of 0.10 and power of 0.8 when the true response rate is 0.20.

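### A positive cohort B would support activity of the triple regimen, not reversal of CAB resistance by dutasteride, because its wording admits patients who may still respond to CAB

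*Protocol article*

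**What the plan says.** The protocol article describes cohort B in three places, each time differently.

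- **Trial design** calls the patients CAB-resistant and gives as examples those treated "in the adjuvant setting with anti-androgens and/or LHRH-analogues or in the palliative R/M setting progressive on first-line therapy".
- **Abstract, Methods** speaks of "patients with disease progression after adjuvant or first-line palliative CAB therapy".
- **Objectives** asks "whether addition of dutasteride counteracts therapy resistance in patients who previously have been treated with anti-hormonal therapy".

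On treatment, Trial design says that these patients "will be enrolled receiving similar therapy to the experimental arm", that is, both CAB components plus dutasteride. There is no control group in cohort B.

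On the test, the sample size section for cohort B says: "The null hypothesis that the true ORR is 5% will be tested against a one-sided alternative". The source of that figure is that "prior data indicate that the response rate on second-line chemotherapy in patients with SGC is 5"%. The regimen is "considered effective and worth of further evaluation if the ORR is at least 20"%. Nine patients enter first, and accrual goes on to 24 if at least one responds. Three or more responses in 24 reject the null. The stated type I error is 0.10 and the stated power is 0.8.

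On CAB itself, Background reports of the earlier phase II trial: "The objective response rate (ORR) was 42"%. The cohort A sample size uses 0.417.

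**The concern.** The label, the population and the null do not match the question. To show that dutasteride reverses resistance, the cohort must consist of patients who would rarely respond to goserelin plus bicalutamide alone, and the null must be the response rate expected on that treatment.

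The wording leaves two gaps on the adjuvant side. Someone who had only an anti-androgen or only an LHRH analogue has not been shown to be resistant to the combination. Someone whose disease returned after adjuvant therapy may have relapsed off treatment. Either may respond to CAB with no help from dutasteride. The 5% benchmark comes from chemotherapy in salivary gland cancer and says nothing about response to CAB in such patients.

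Only three responses are needed, so a few still-sensitive patients could decide the result, and it could then be read as evidence that dutasteride overcomes resistance.

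**Working it through.** **Step 1. Who can enter.** The adjuvant example in Trial design joins the two drug classes by and/or, so one class suffices. The abstract's background section defines CAB itself with the same and/or, so its use of the term CAB does not close this gap. The abstract's word for the timing of progression is after, which covers relapse once adjuvant treatment has stopped. The palliative example in Trial design requires progression on first-line therapy, so the off-treatment point does not reach that group.

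**Step 2. Reproduce the stated design.** Inputs from the cohort B sample size section: n1 = 9, continue if at least 1 responds; n = 24, success if at least 3 respond; p0 = 0.05, p1 = 0.20.

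P(success | p) = Σ over x ≥ 1 of P(X1 = x) × P(X2 ≥ 3 − x), with X1 ~ Bin(9, p) and X2 ~ Bin(15, p).

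- p = 0.05: 0.2985 × 0.1710 + 0.0629 × 0.5367 + 0.0084 = 0.093
- p = 0.20: 0.3020 × 0.8329 + 0.3020 × 0.9648 + 0.2618 = 0.805

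Both agree with the stated 0.10 (a ceiling) and 0.8. A search over designs returns the same optimal design. The arithmetic of the plan is right.

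**Step 3. Chance of success when dutasteride adds nothing.** Let f be the share of enrolled patients who are still CAB-sensitive and q their response rate to CAB. Let the rest respond at the plan's 5%. Then p = f·q + (1 − f)·0.05.

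The article gives neither f nor q, so both are assumptions and are varied. The upper value of q is 41.7%, the CAB-naïve rate; patients with earlier hormonal exposure are unlikely to exceed it.

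Example, f = 20% and q = 41.7%: p = 0.2 × 0.417 + 0.8 × 0.05 = 0.1234. P(success) = 0.3872 × 0.5685 + 0.2180 × 0.8613 + 0.0891 = 0.497.

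| q | f = 10% | f = 20% | f = 30% |
|---|---|---|---|
| 15% (assumed) | 0.14 | 0.19 | 0.25 |
| 20% (assumed) | 0.16 | 0.25 | 0.34 |
| 30% (assumed) | 0.22 | 0.36 | 0.51 |
| 41.7% (CAB-naïve rate, upper bound) | 0.29 | 0.50 | 0.67 |

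With f = 0 the figure is 0.093. Every cell exceeds the stated 0.10. At the upper bound, the cohort would reach the 20% target without dutasteride when f = (0.20 − 0.05)/(0.417 − 0.05) = 0.15/0.367, about 41%.

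**Step 4. What a rejection means.** The sample size section draws its conclusion about the triple therapy, and that conclusion survives. Objectives draws one about adding dutasteride to overcome resistance. That does not follow unless f is close to zero, and the published wording does not secure this.

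**The case against.** The best defence has four parts.

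- **This is a condensed article.** The parenthesis in Trial design gives examples, and Eligibility criteria lists no cohort-specific rules. The full protocol may define resistance, progression on treatment and time since last dose. That is fair, and no missing criterion is alleged here. But the and/or example and progression after adjuvant therapy are positive statements of who may enter. They fit poorly with the label, and the three descriptions differ.
- **The rule is a regimen-level screen.** Success is declared for the triple therapy, which is then worth further study, and the statistical methods section reports cohort B descriptively. A disclosed benchmark from another second-line option is a usual choice for that purpose. This stands, and it is why the Simon rule can be kept. It does not rescue the resistance claim in Objectives and in the abstract.
- **Progression after CAB may only mean progression following exposure.** That is possible. The wording allows both readings, which is a reason to reconcile it.
- **The size is assumed.** It is, and the lower rows of the table are modest.

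A reader might also infer that closing cohort A, after two inclusions, removed the benchmark for cohort B. The article does not support this. Cohort A is CAB-naïve, so even a full control arm could not have estimated response to CAB in previously exposed patients.

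**Conclusion.** The point holds as a limit on what cohort B can conclude. Its described population may include patients who respond to CAB itself, so at least 3 responses in 24 against a 5% null would support at most activity of goserelin, bicalutamide and dutasteride together. It would not show that dutasteride counteracts resistance.

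Under no dutasteride effect, the chance of a positive cohort ranges from 0.14 (f = 10%, q = 15%) to 0.67 (f = 30%, q = 41.7%). This rests on assumed f and q and on 5% response in resistant patients. A reader might take 0.29 to 0.67 as the trial's actual false-positive rate. The documents do not support that, because those figures use the CAB-naïve response rate as an upper bound and the share of sensitive patients is unknown. Nor is the two-stage design miscalculated; its stated error rates reproduce.

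**What to change.** 1. Reconcile the descriptions of cohort B in the abstract, Objectives and Trial design, so that they agree on which prior agents count and whether progression must have occurred on treatment.
2. Keep the 9 and 24 patient rules as the screen of the regimen, and state that the conclusion concerns the regimen.
3. Before responses are reviewed, prespecify that the objective response rate is also reported separately for (a) patients with documented progression while receiving both an LHRH agonist and an AR antagonist and (b) all others. Base the split on recorded prior components and time since last dose. The trial is open-label, so the classification must not be made after responses are known.
4. Restrict any statement that dutasteride counteracts or overcomes resistance to group (a).

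The cost is amendment wording and, if not already captured, two data items per patient. The downside is a narrower conclusion and wider intervals: if half of the 24 fell in group (a), the interval would be about √(24/12) = 1.4 times as wide at the same response rate. Counting only group (a) toward the Simon rule would be stricter. In a rare disease with a cap of 24, however, it would slow accrual or require a higher cap, so separate reporting is the more practical choice.

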**Fig. 2 Fig2:**
[figure not shown]
DUCT Study design and enrolment. Abbreviations: AR, Androgen receptor; CAB, Combined androgen blockade; CBR, Clinical benefit rate; DoR, Duration of Response; ECOG, Eastern Cooperative Oncology Group; OD, Once daily; ORR, Objective response rate; OS, Overall survival; PFS, Progression-free survival; QoL, Quality of Life; R/M, Recurrent and/or metastatic

### Eligibility criteria

To be eligible for enrolment, subjects must meet the following inclusion criteria: capable of and willing to prove written informed consent; having a confirmed pathologically/histologically diagnosis of AR-positive R/M SDC; measurable disease per RECIST v1.1; age of 18 years or older; Eastern Cooperative Oncology Group (ECOG) performance status of 0 or 1 [20]; and demonstrating adequate bone marrow, liver, renal, and cardiac functions.

Exclusion criteria for trial participation encompass: recent use (< 6 months) of 5-alpha reductase inhibitors; prior allergic reactions to compounds such as goserelin, bicalutamide and/or dutasteride as well as to peanut and/or soy; inadequate swallowing capacity; long QT-syndrome; failure to implement adequate contraceptive measures for patients with reproductive potential; pregnancy or lactation; uncontrolled cardiovascular disorders or hypertension, recent stroke, or myocardial infarction, and serious active infections; any other concurrent experimental treatments; curative radiation therapy within 4 weeks before inclusion; or palliative radiation therapy 1 week before inclusion.

